## Abstract

**Background:** D/deaf and hard of hearing populations are at higher risk for experiencing physical and mental health problems compared to hearing populations. In addition, they commonly encounter barriers to accessing and benefiting from health services, which largely stem from challenges they face in communicating with healthcare providers. Healthcare providers commonly lack tailored communication skills in caring for D/deaf and hard of hearing populations, which lead to difficulties and dissatisfaction for both staff and D/deaf and hard of hearing communities. This research project aims to develop and evaluate a capacity-building intervention for healthcare providers with the goal of increasing their awareness of D/deaf and hard of hearing individuals' experiences with the healthcare system, their distinct needs, and improving their capacity to communicate effectively with this patient population.

**Methods:** This research project features a participative action research design using qualitative and quantitative methods. Consistent with participative action research, the study will actively involve the target populations, key stakeholders and representative associations. The intervention will be developed and tested through iterative phases. The Integrated Model of Training Evaluation and Effectiveness will guide prospective evaluation of the intervention. The latter will involve qualitative and quantitative assessments in participants before and after the intervention and at 6-months follow-up.

**Discussion:** Results will contribute to research aimed at decreasing barriers to accessing and benefiting from healthcare services for D/deaf and hard of hearing individuals. Findings will be presented to representative associations and political authorities, as well as disseminated at research conferences and in peer-reviewed journals.

## Introduction

Around 466 million people experience some type of hearing loss worldwide [i.e., hearing loss > 40 and 30 dB in the better hearing ear in adults and children, respectively; (1)] and this number may reach 900 million by 2050. This group includes D/deaf and hard of hearing individuals who self-identify themselves as part of the hearing population (lowercase *d*) or as part of the Deaf community (with a capital *D*), a minority community with its own culture. Among these groups, Deaf community communicates with sign language, whereas deaf and hard of hearing individuals communicate with vocal language while using hearing assistive devices or communication tools stemming from the local language. In Switzerland, more than one in 100 individuals (0.1%) are D/deaf, whereas up to 13% of the population are hard of hearing (2, 3).

Epidemiological studies have documented a wide range of health inequities in D/deaf and hard of hearing populations. Findings indicate for instance that they are more likely to engage in risky behaviors than hearing populations [e.g., heavy alcohol use, unsafe sex; (4, 5)]. Furthermore, D/deaf and hard of hearing populations are at higher risk of experiencing mental [e.g., depression; (6–8)], and physical health problems [e.g., chronic diseases; (7, 9–11)] comparing to hearing populations.

Alarmingly, despite their need of services, D/deaf and hard of hearing populations experience significant barriers when accessing healthcare services that negatively impact their access to care and health outcomes (12, 13). The most significant barriers stem from communication challenges commonly experienced by both D/deaf and hard of hearing populations, and healthcare providers during clinical encounters (14–16). Examples of challenges include using complex medical terminology or drug prescription instructions, which are not understood by the patient, potentially leading to preventable adverse events (17). Communication and language difficulties also lead to unsatisfactory patient-provider relationships (18, 19). A recent survey conducted in 21 public and private hospitals and ambulatory care centers in the *Canton of Vaud* (a French-speaking region of Switzerland comprising ~10% of the Swiss population) documented healthcare providers' difficulties in communicating with the target population (20). Similar findings were yielded in another study conducted in the same region that also highlighted dissatisfaction regarding healthcare in the target population (21).

Healthcare providers commonly lack tailored communication skills, knowledge about D/deaf culture and D/deaf and hard of hearing individuals' experience and specific needs (16, 18, 20, 22, 23). This is critical because lack of knowledge has been associated with decreased access to healthcare among individuals with hearing loss (12, 15, 24, 25). Despite its importance, there is currently no formal capacity-building intervention for healthcare providers in the *Canton of Vaud* in Switzerland aimed at raising awareness about the barriers faced by D/deaf and hard of hearing individuals' in the healthcare system and improving communication (21).

Healthcare providers may use existing educational support offering practical advice and guidance on how communicating with D/deaf and hard of hearing patients [e.g., (26)]. However, although helpful for interested professionals, this education support is likely to reach a very limited number of healthcare providers who are typically overworked. Developing and implementing interventions in the healthcare system is critical to reach a broader audience. However, scarce research to date focused on developing and evaluating training to improve healthcare providers' communications skills with these populations. To the best of the authors' knowledge, only a handful of previous studies focused on developing such interventions and they involved students [i.e., medical and pharmacist students; (27, 28)]. These studies aimed to develop a role-reversal exercise in which students were the patients and Deaf volunteers the medical staff. Findings documented a high level of satisfaction among students, with up to 97% reporting that this experience would have an impact on their attitudes and behaviors in the future (27, 28). However, no longitudinal evaluation was conducted and this program was not tailored to healthcare providers already in the field.

Given the lack of research in this area and the negative experience of D/deaf and hard of hearing individuals while receiving healthcare, an important next step for research is to develop and test interventions tailored to healthcare providers. In response, this research project aims to develop and evaluate a capacity building intervention for healthcare providers to improve their communication skills and increase their awareness of D/deaf and hard of hearing individuals' experience and specific communication needs. The research project will feature a participative action research design. Participative research is particularly critical when it comes to addressing health inequities in minority groups (29). Participative-based research aims at conducting research with communities in a collaborative and equitable partnership, allowing power-sharing process, and building on strengths and resources of the communities (30). Using this design will ensure to develop an intervention that will rely on strengths and resources within the involved community and that will be tailored to their specific needs and expectations. Accordingly, both the content and the format of the capacity building intervention will be developed together with the target populations, key stakeholders and representative associations. The resulting capacity building intervention will be evaluated among healthcare providers (e.g., reception staff, physicians, nurses, pharmacists) using a qualitative and quantitative two-fold measure. First, the intervention content and design (i.e., satisfaction and perception of the intervention content, quality and appropriateness) will be evaluated both quantitatively and qualitatively after receiving the intervention. Second, perception of self-efficacy regarding the skills taught during the intervention and organizational payoffs (i.e., frequency of use or intention to use the skills taught during the intervention) will be measured quantitatively before the intervention, directly after and 6 months later to evaluate changes in participants after receiving the intervention.

## Methods and Analysis

### Setting and Study Design

#### Setting

This research project^1^ will take place at the Center for Primary Care and Public Health in Lausanne (Unisanté) in collaboration with several medical institutions involved with the target population in the *Canton of Vaud*, D/deaf and hard of hearing representative associations and D/deaf and hard of hearing individuals. Consistent with participative research, the research team will be multidisciplinary, including staff from the medical, linguistic and psychology sciences, and will include D/deaf, hard of hearing and hearing staff.

#### Action Research Design

This project will feature an action research design using qualitative and quantitative methods. Action research is aimed at solving practical concrete problems, enhancing staff knowledge and skills, empowering participants and improving the quality of care (31). The action research design features five cyclical and iterative phases (see Figure 1): (1) *Problem identification* (identify and define the problem); (2) *Action planning* (design the action based on phase 1 data); (3) *Implementation of the action*; (4) *Evaluation of the action*; and (5) *Learning and refinement* (i.e., action refinement and dissemination) (32).

**Figure 1 F1:**
[figure not shown]
Research project timeline by research action phases.

#### Patient and Public Involvement

Action research allows for a bottom-up approach, involving the target population, the stakeholders and the researchers to better understand and address an identified problem through active collaboration (33). Accordingly, the research team will include three D/deaf and hard of hearing research collaborators who will be involved in the intervention development. Together with the hearing research staff, they will develop the content and format of the intervention based on results yielded in Phase 1. Furthermore, the three D/deaf and hard of hearing research staff will be the trainers during the intervention. Finally, they will be involved as co-authors in findings' dissemination related to intervention development and evaluation (i.e., presentations, critical review of manuscripts and co-authorship). Participative research will also be operationalized through establishing an advisory committee including D/deaf and hard of hearing individuals, association representatives, involved stakeholders and experts. This committee will provide ongoing feedback and advice to the research team and will also participate in the intervention development.

As shown in this Figure 1, the project started in November 2019 and is scheduled to be completed in 2 years and 2 months over five phases of research action.

### Study Procedures in Phase 1: Problem Identification

#### Institutional Partnerships

The research team previously created partnerships with 5 medical institutions involved with the target population in the *Canton of Vaud* including clinical units from the home institution; geriatric acute services and geriatric rehabilitation unit at Lausanne University Hospital, the local nursing home association (HévivA) and the local home support association (AVASAD). Heads of partner institutions will provide support to the research team to promote the research study within the institutions.

#### Advisory Committee

The research team previously formed an advisory committee including two D/deaf and one hard of hearing individuals; two healthcare providers with experience with the target population; a representative of administrative healthcare staff; representatives from D/deaf and hard of hearing-focused associations; and one interpreter in French sign language. The committee will be involved in the development of the intervention and will provide ongoing feedback through regular meetings.

#### Phase 1 Data Collection

The research team will conduct qualitative assessments with healthcare staff and the target population to clarify the barriers, needs and gather advice on the intervention content being developed. This phase will aim to understand and describe the issue and needs from the perspective of the target population.

#### Healthcare Staff Participants

Healthcare providers and administrative staff from the partner institutions will be invited to participate in one-on-one semi-structured interviews. Inclusion criteria include being 18 years or older and having cared for or assisted at least one D/deaf or a hard of hearing individual in a healthcare work environment. A group characteristics sampling per quotas by functions (i.e., physicians, nurses, other) was selected as purposeful sampling. We expect that between 5 to 10 interviews per type of healthcare staff will be necessary to achieve saturation, leading to around 15–30 interviews.

#### D/deaf and Hard of Hearing Individuals

Inclusion criteria include being 18 years or older and being D/deaf or hard of hearing. A group characteristics sampling per quotas by hearing loss (i.e., D/deaf vs. hard of hearing) was selected as purposeful sampling. We added a group characteristics sampling per quotas by age (i.e., 18–64 vs. 65 and older) for hard of hearing individuals to account for age-related hard of hearing (i.e., around 65) vs. more precocious forms of hard of hearing. We expect that between 5 to 10 interviews per quota will be necessary to achieve saturation, leading to 15–30 interviews.

Recruitment will be conducted with the support of D/deaf and hard of hearing-related associations and within the participating nursing home. In addition, a short video promoting study participation in sign language will be posted on the websites of D/deaf associations. When first getting in touch with interested participants, the research team will ask them to indicate their preferred mode of communication for the one-on-one semi-structured interviews. When necessary, the research staff will conduct semi-structured interviews with French sign language interpreters.

#### Phase 1 Qualitative Analysis

Semi-structured interviews will be audio recorded and transcribed *verbatim*. Personal identifiable information will be removed from transcripts prior to data coding. We will use conventional content analysis to analyze data (34). The research team will code the data using a constant comparative process (35). Initial coding will be conducted separately using line-by-line technique, whereby coders narrate the actions occurring in the data. Following independently initial coding, we will create a codebook in consensus meetings, pooling incident-by-incident codes and removing collapsing idiosyncratic or redundant codes. Next, we will use the codebook to independently double-code 10% of the sessions. After reaching adequate intercoder consistency (80%), a single coder will code the remaining sessions. Finally, feedback from the advisory committee will serve as a means of assessing fit and resonance of findings.

This process will be conducted independently with data yielded among healthcare and administrative staff and with data collected in the target population. Qualitative analysis will be conducted using Atlas.ti software.

### Study Procedures in Phase 2: Action Planning

This phase will start with workshop involving the advisory committee aimed at defining a concept for the capacity building intervention and creating potential solutions. The research team will then rapidly develop a prototype intervention, based on ideas generating through the workshop and qualitative findings from Phase 1. The research team will organize the first capacity building intervention that will be tested in the next phase (Phase 3) through partner institutions.

### Study Procedures in Phase 3: Action Implementation

A first round of the capacity building intervention will take place in the partner institutions. We expect around 2 participants from each partner institution to participate in the first round of testing. After the intervention, participants will complete a short questionnaire and participate in a focus group to evaluate intervention's content, quality and appropriateness and assess their overall satisfaction (see Table 1 and Phase 4 for more details regarding the evaluation).

**Table 1 T1:** Summary of measures by action research phase.

**Components**	**Tool**	**Participants**	**Timing of assessment**
**Phase 1: Problem Identification**			
Needs analysis	Qualitative assessment (one-on-one semi-structured interviews)	Healthcare staff (*n* ~ 15) D/deaf and hard of hearing individuals (*n* ~ 15)	Beginning of Phase 1
Qualitative assessment (semi-structured interviews)	Healthcare staff (*n* ~ 15) D/deaf and hard of hearing individuals (*n* ~ 15)	Beginning of Phase 1	
**Phase 2: Action Planning**			
No measure			
**Phases 3 and 4: Action implementation and Evaluation**			
**Intervention Testing: Round 1**			
**Participants' reactions**: perception of intervention's content, quality and appropriateness, overall satisfaction	Adapted IMTEE questionnaire^*a*^ Qualitative assessment (focus group)	Healthcare staff receiving intervention 1 (*n* ~ 10)	After intervention 1
**Intervention Testing: Round 2**			
**Participants' reactions**: perception of intervention's content, quality and appropriateness, overall satisfaction	Adapted IMTEE questionnaire^a^ Qualitative assessment (focus group)	Healthcare staff receiving intervention 2 (*n* ~ 50)	T1^d^ T1
**Changes in participants**: perception of self-efficacy, attitudes toward skills taught during the intervention	Adapted IMTEE questionnaire^b^ Qualitative assessment (focus group)		T0, T1, T2^d^ T1
**Organizational payoffs**: frequency of use or intention to use skills taught in the intervention	Adapted IMTEE questionnaire^c^ Qualitative assessment (focus group)		T0, T1, T2^d^ T1

a *Participants will be asked to rate their satisfaction regarding the intervention and to evaluate its content, quality, and appropriateness using a 5-point Likert scale, ranging from 1 (not satisfied at all/improvement needed) to 5 (completely satisfied/very good)*.

b *Participants will be asked to indicate the extent to which they agree with items using a 5-point Likert-scale ranging from 1 (strongly disagree) to 6 (strongly agree)*.

c *To evaluate intentions to use the newly acquired skills, we will ask participants to indicate the extent to which they agree or disagree with statements using a 6-point Likert scale ranging from 1 (strongly disagree) to 6 (strongly agree). Regarding frequency of use, participants will be asked to indicate how often over the past 6 months they applied specific strategies, using a 5-point Likert scale ranging from 1 (never) to 5 (most of the time)*.

d *T0 = before intervention 2; T1 = just after intervention 2; T2 = 6 months after intervention 2*.

A second improved version of the intervention will then be developed based on the findings yielded in the first round of testing and through discussions with the advisory committee. A second round of the intervention will be organized to test it (involving new participants); for this second round, we expect including between 5 and 15 participants by partner institution (*n* ~ 50). The same methods will be applied to evaluate the improved version of the intervention.

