##### Organizational Payoffs

We will use 6–10 items to assess the intention to use and use frequency of the newly acquired skills use over the past 6 months (37, 38) at T0, T1, and T2.

These dimensions will also be evaluated qualitatively through focus group at T1.

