#### Quantitative and Qualitative Analysis (Second Round of Intervention)

Quantitative data will be screened for missing cases, outliers, and normality of distributions using descriptive statistics. Main analyses will comprise multilevel models (i.e., MLM, mixed effects model) (39). MLM examines the effect of time (after receiving intervention) on dependent variables (changes in participants, organizational payoffs). We will include sources of random variability at the group level accounting for between-group differences and another random effects for the individual accounting for within-person differences in the repeated measures. MLM will be adjusted for demographic variables, role (i.e., nurse, physician, administrative staff) and years of experience. Analyses will be conducted using STATA. The significance level will be set at *p* = 0.05.

Qualitative data yielded from focus groups will mirror the analysis methods used in Phase 1.

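### Use frequency is scored from 'never' with no described measure of opportunity, so staff who met no D/deaf or hard of hearing patient count as non-users; this dilutes, and can distort, the T0–T2 change

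*Protocol article*

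**What the plan says.** Table 1, footnote c, of the protocol article defines the use-frequency question as "how often over the past 6 months they applied specific strategies", answered "using a 5-point Likert scale ranging from 1 (never) to 5 (most of the time"). The section Organizational Payoffs gives its length and pairing with intention: "We will use 6–10 items to assess the intention to use and use frequency of the newly acquired skills use over the past 6 months", at T0, T1 and T2.

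The outcome enters the main model. In the analysis section for the second round, "MLM examines the effect of time (after receiving intervention) on dependent variables (changes in participants, organizational payoffs"). The covariates are also fixed there: "MLM will be adjusted for demographic variables, role (i.e., nurse, physician, administrative staff) and years of experience".

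On who takes part, the Phase 1 section Healthcare Staff Participants requires interviewees to meet the criterion "having cared for or assisted at least one D/deaf or a hard of hearing individual in a healthcare work environment". No such criterion is stated for round 2, which enrols new people: "for this second round, we expect including between 5 and 15 participants by partner institution", about 50 in all. The Introduction lists reception staff and pharmacists among the staff to be evaluated.

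**The concern.** Using a communication strategy requires a patient to use it with. The item asks about behaviour over a fixed window but, as described, does not record whether that window contained a D/deaf or hard of hearing patient. Two different states then share the score of 1: no relevant patient seen, and relevant patients seen but nothing applied. A respondent who leaves the item blank instead makes missingness depend on caseload.

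Use frequency is the only outcome that reports behaviour rather than opinion or intention, and it is read as change within person without a control group. The T0 and T2 questions cover different 6-month windows. The individual random effect absorbs only stable differences between people, and role and years of experience do not track a person's contacts from one window to the next. The Challenges and Limitations section relies on qualitative data to complement the quantitative findings, but the focus groups take place at T1, before the follow-up period in which the skills would be used. Information on opportunity that is not collected at T0 can hardly be recovered later.

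**Working it through.** The article gives no effect size, standard deviation or expected use score, so there is no stated figure to reproduce. The check has two parts.

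**1. Is opportunity captured anywhere?**

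| Place in the article | What it covers | Contact captured? |
|---|---|---|
| Table 1, footnote c | 5-point scale, past 6 months | No such answer described |
| Intervention Content and Design; Changes in Participants; Organizational Payoffs | Reactions, self-efficacy, knowledge, attitudes, intention, use | No |
| Second-round analysis | Demographics, role, years of experience | No |
| Round 2 participants | New participants, 5 to 15 per institution | No criterion stated |
| Phase 1 interviewees | At least one relevant patient | Yes, but another sample and no 6-month window |

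**2. What would the omission do to the score?**

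Let q be the share with no relevant contact in the window (scored 1) and m the mean score among those with contact. Then

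mean = (1 − q) × m + q × 1,

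and the observed change is (1 − q2)(m2 − 1) − (1 − q0)(m0 − 1). All values of q and m below are assumptions.

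*(a) Dilution: same q in both windows, true rise from 2.5 to 3.0.* The observed change is (1 − q) × 0.50.

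| q | Observed change |
|---|---|
| 10% | 0.45 |
| 20% | 0.40 |
| 30% | 0.35 |
| 40% | 0.30 |

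*(b) Spurious change: behaviour constant at m.* The observed change is (q0 − q2) × (m − 1).

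- m = 3.0, q from 20% to 10%: 0.10 × 2 = +0.20
- m = 3.0, q from 30% to 10%: 0.20 × 2 = +0.40
- m = 3.0, q from 10% to 30%: −0.20 × 2 = −0.40
- q from 30% to 10% with m = 2.5 or 3.5: 0.20 × 1.5 = +0.30, or 0.20 × 2.5 = +0.50

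*(c) Masking: true rise from 2.5 to 3.0 while q goes from 10% to 30%.* T0 mean: 0.9 × 2.5 + 0.1 = 2.35. T2 mean: 0.7 × 3.0 + 0.3 = 2.40. The observed change is 0.05 instead of 0.50.

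*(d) How likely is zero contact?* If patients are independent draws at prevalence p, the chance of none among n patients is (1 − p)^n.

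- Hard of hearing, at the Introduction's upper figure of 13%: 0.87^10 = 25%, 0.87^20 = 6%, 0.87^50 = 0.1%.
- D/deaf: the Introduction gives both one in 100 and 0.1%. Among 100 patients, 0.99^100 = 37% and 0.999^100 = 90%.

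Zero contact with hard of hearing patients is therefore unlikely for staff who see many patients. It is plausible for low-contact roles, and for strategies that apply only with signing patients.

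**The case against.** The strongest reply is that the questionnaire did not yet exist. The Phase 4 section says it will be developed to fit the intervention and pre-tested in 10 providers, and a condensed article need not list filter questions or not-applicable boxes. This stands in part. A reader might infer that the instrument forces everyone without contact to tick 'never', but the article shows only the scale length, its end anchors and the dimensions measured, so that cannot be claimed of the final form. The point survives because scale, window, dimensions and covariates are already laid down and none of them captures contact.

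Second, the mechanism is narrow. The top anchor, 'most of the time', reads as a proportion of occasions, so among staff with some contact a larger caseload need not raise the score. This stands: the mixing acts mainly through people with no contact.

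Third, the partners were chosen for their involvement with these patients and include acute geriatric care, geriatric rehabilitation, nursing homes and home support. This stands for hard of hearing patients and limits the likely size. It describes institutions, though, not each participant, and it says little about signing patients.

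Fourth, a false change requires the no-contact share to shift between windows, and the article reports no such shift. This also stands; a constant share only dilutes.

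Fifth, intention, self-efficacy, knowledge and attitudes do not depend on opportunity, and the article presents the study as a first evaluation, leaving efficacy to a later randomised trial. That limits the consequence for the study as a whole, but does not make the use item easier to interpret.

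**Conclusion.** The point holds as a measurement weakness in one outcome. As described, the use-frequency item cannot separate non-use from lack of opportunity, and nothing else in the described plan supplies that information. The consequence is a diluted T0–T2 change, with a spurious or masked change possible if the no-contact share differs between windows.

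The size is unknown. The figures from 0.05 to 0.50 points rest on assumed shares and scores and show only how the mechanism works. In the geriatric, nursing-home and home-support partners the effect may be modest; it is most plausible for low-contact roles and strategies specific to signing patients.

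A reader might go further and conclude that any observed change in use would mainly reflect caseload. The documents do not support that: they give no contact rates and no evidence of a shift, and the settings make widespread zero contact with hard of hearing patients unlikely.

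**What to change.** When the questionnaire is finalised, before T0, with the planned pre-test as the natural occasion:

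1. Add one item at T0 and T2 on how many D/deaf and how many hard of hearing patients the respondent met in the past 6 months, recorded separately (for example 0, 1–5, more than 5).
2. Add a 'no opportunity' option for each strategy, coded as not applicable rather than 'never'.
3. Report the no-contact share at T0 and T2.
4. Show the all-participant use-frequency result beside a sensitivity analysis limited to, or adjusted for, contact.

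The contact-based analysis should not replace the all-participant result. Contact at T2 is reported after training that aims to raise awareness, so trained staff may recognise more hard of hearing patients. Restricting on it conditions on something the intervention can change, and the report should say so.

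The cost is one extra item, one answer option and fewer usable responses for this outcome. As an illustration, if 30% had no contact at T0 and 20% at T2, independently, 0.7 × 0.8 = 56% would have contact in both windows, about 28 of 50.
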